## 3.5 Self-administered medication adherence questionnaire

The objective of this small exploratory study is to obtain a rapid assessment of patients’ medication adherence and beliefs. A secondary objective of this small-scale study is to explore the feasibility of employing this questionnaire in terms of time, usefulness and performance. This rapid assessment tool should provide insight into medication adherence while imposing minimal burden on respondent and data collector and thus may prove useful for repeated administration within the Irbid programme and more broadly within MSF.

### 3.5.1 Adherence questionnaire methodology

A self-administered questionnaire using translated existing tools will explore patients’ behaviours and beliefs regarding medication adherence.

### 3.5.2 Adherence questionnaire population

The study location will be the two MSF-OCA supported clinics in Irbid city, northern Jordan. Any patient enrolled in either clinic according the criteria described in section 3.4.1, aged eighteen years or older, has attended the clinic for over one month and has had at least one admission and one review medical consultation, is eligible to take part in the adherence survey.

### 3.5.3 Adherence questionnaire eligibility criteria, recruitment and sampling

A randomly selected sample (e.g. through randomisation of patient numbers) of MSF patients aged eighteen years or older attending either MSF clinic over a two–week data collection period, will be approached to fill the 17-item questionnaire, in order to give a sample size of 300 (based on previous studies ^25^). Questionnaires are presented in Arabic and should take approximately fifteen minutes to complete. The Arabic-fluent data collector will administer the questionnaire to patients with limited literacy and this will be recorded on the questionnaire.

### 3.5.5 Adherence questionnaire data management

Data will be anonymised and entered into a purpose-designed, password-protected Excel database by a trained data entry operator.

### 3.5.6 Adherence questionnaire data analysis

The originators of these scales require that they are analysed and reported in accordance with their instructions in order to promote uniformity and facilitate comparison of findings across studies. Results will be analysed using basic descriptive statistics. Analysis will include proportions and means, presented with 95% confidence intervals (95%CI). Adherence rates will be compared using multiple linear regression to explore the effect of age, gender, civil status, education status, type and number of morbidities, number of medications and whether administered by self or by the data collector.

## 3.6 Cross-sectional household survey data analysis

This survey, undertaken in June and July 2016, was led by the MSF-OCA Irbid NCD Project team and received MSF-OCA ERB approval. The primary objective was to determine the level of access to health care services for Syrian refugees living out-of-camp in Irbid governorate, Jordan. Secondary objectives included: a) describing the socio-demographic characteristics, economic circumstances and health care utilisation of the surveyed population, b) estimating coverage of essential health services, particularly MSF-provided services and c) estimating health service needs and barriers to health care access amongst the surveyed population.

### 3.6.1 Household survey population

The study population consisted of UNHCR-registered and unregistered Syrian refugees living outside of official camp settings in Irbid governorate.

### 3.6.2 Household survey eligibility criteria and sampling

A person was included in survey if he or she met the following criteria: living in a selected household; arrived in Jordan in or after January 2012 and at least 6 months prior to the survey interview; and permission had been granted to take part in the interview by the household head. To be eligible to answer specific health questions the following criteria were also required: general health: adult aged 18 years or older; NCD care: adult 18 years or older and living with one or more of the following conditions: hypertension, CVD, diabetes type I or II, chronic respiratory disease, thyroid disease or cancer; child health: under five years of age; antenatal care: female aged fifteen to forty nine years and had given birth to a live infant in the previous twelve months in Jordan.

Sample size was calculated using OpenEpi and STATA 13 (StataCorp, College Station, TX, USA), using reference values based on UNHCR household surveys^29^. An estimated number of 2616 households needed to be interviewed, sampled in 327 clusters of eight households. A two-stage cluster sampling methodology was adapted from the standardised methodology recommended by the WHO (Henderson and Sundaresan 1982).

### 3.6.3 Household survey data collection and management

Data were collected by trained interviewers using an electronic tablet-based survey tool. Data were uploaded daily to an off-site server using secured MSF Wi-Fi. Aggregate data were exported daily for back-up and were stored on a password-protected computer.

### 3.6.4 Household survey data analysis

Primary data analysis has been completed using descriptive statistics and multivariate regression modelling and will be reported elsewhere. Secondary analysis of the pre-existing data using RStudio v1.0.136 (RStudio, Boston, MA 02210, USA) will determine the number of people eligible for and receiving NCD care, the geographical reach of the programme and the target population’s knowledge of MSF. Results will be analysed using basic descriptive statistics, including Pearson’s χ2 test for proportions and will be presented with p-values.

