**Methods:**

*Design*: A mixed-methods design will be used, based upon the RE-AIM framework (see <http://www.re-aim.hnfe.vt.edu/>). Objective 1 (Reach) will refer to a pre-existing dataset from a random cross-sectional population-level household survey previously conducted by MSF for separate purposes; routine cohort data from two MSF clinics in Irbid; and qualitative data from focus groups, semi-structured and key informant interviews. Objective 2 (Effectiveness) will use a cohort study design of chronic disease patients at the MSF-run clinics in Irbid. It will use routine clinic data to explore trends in clinical outcomes and other quality of care indicators, which occurred during MSF’s implementation of this NCD care model in Irbid. It will also include descriptive analysis of total and unit programmatic costs. Objective 3 (Adoption/acceptance) will use qualitative data to explore issues around adoption and acceptance of the model components through participant observation, focus group discussions and semi-structured interviews with patients, staff and key stakeholders. A small exploratory study to develop and test a short survey of self-reported medication adherence and beliefs will also be undertaken. Objective 4 (Implementation) will use routine cohort data, clinical audit, participant observation, routine costing data and qualitative data (as described above). Objective 5 (Maintenance) uses routine cohort data, qualitative data (as described above) and data on medical supplies, costs and staff time estimates.

*Study participants:* The pre-existing cross-sectional health service access survey included Syrian refugees households living outside of camp settings in Irbid governorate, selected using a two-stage cluster design. For the routine cohort data, all patients six years and older with confirmed NCDs attending the two MSF clinics in Irbid more than once, will be included (using patient records from January 2015 to December 2016). For the qualitative research, respondents will be purposively selected patients and/or health workers, past and present, from the two MSF clinics in Irbid. Key stakeholder interviews will include staff from MSF and other NGOs, Jordanian MoH staff and community leaders. For the medication adherence survey, a random sample of 300 consenting service users attending the MSF clinic will be selected.

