*Data collection*: Household survey data were previously collected by trained interviewers using an electronic tablet-based survey tool and uploaded to a password-protected server. Trained data clerks will collect routine cohort data from routine patient records and will input this data daily into a predesigned database. Clinical audit data will be collected on a paper-based checklist from routine patient records and entered into a purpose-designed Excel spreadsheet. Cost data will be obtained from accounting records, supply orders and staff observation. Qualitative data will be collected by trained interviewers using topic guides. The adherence survey will utilise adapted pre-existing self-report medication adherence and beliefs measures with data entered into a purpose-designed Excel spreadsheet.

*Data analysis:* Secondary analysis of the pre-existing household survey data will use descriptive methods and multivariate regression modelling. For the cohort study, descriptive analysis and multivariate logistic regression analysis will be used to explore the clinical outcome trends, complication rates, quality of care and guideline adherence that occurred during implementation of this model. Data from the clinical audit and from the adherence survey will be analysed using descriptive statistics. Costing analysis will describe total and unit costs and will compare cost levels and trends across different time periods as new programmatic elements were added. The qualitative research will use thematic analysis. Qualitative and quantitative data from the various data sources will be triangulated.

**Ethical considerations:** This study protocol will be submitted to the MSF Ethics Review Board and LSHTM Ethics Committee for ethics clearance. Written authorisation to implement the study will also be obtained from the MoH of Jordan.

**Dissemination:** Ongoing data from the study will be shared with local, national (including the Jordanian MoH) and international stakeholders every 6 months in order to inform and improve the delivery of NCD care by MSF and other public health agencies in the study area. Outputs will include reports and peer-reviewed academic publications and presentations at key conferences and workshops.

Table of Contents

Key data 2

List of acronyms 3

Executive Summary 4

1. Background 12

1.1 MSF Model of NCD Care in Irbid 13

1.1.1 NCD Service 14

1.1.2 Patient circuit 15

1.1.3 MSF NCD Clinical Guidelines 18

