### 3.4.2 Cohort study main outcome measures

The principal **clinical outcome measures** for patients in the cohort are:

DM: HbA1c < 7 or 8%; proportion of patients meeting individualised target at last visit within the reporting period and trend from baseline

Hypertension: BP < 140/90 mmHg: proportion of patients at target at last visit within the reporting period and trend from baseline

Cardiovascular disease: change in total cholesterol level from baseline

Asthma / COPD: Free from exacerbations / admissions in last six months

The principal **quality of care outcome measures** are the following:

Number/ % of active patients with CVD prescribed a statin during reporting period

Number/ % of patients with CVD prescribed aspirin during reporting period

Number/ % of patients with CVD prescribed at least one anti-hypertensive during reporting period

Number/% of patients with COPD/asthma with inhaler technique check documented

Number/ % of times when appropriate clinical action taken based on clinical or laboratory findings according to guideline (see Annexe 2e for detail)

Description of trends and patient characteristics in programme defaulters and deaths

Proportion of recommended referrals to other services that are appropriate as per guideline

Death is defined as confirmed death reported by family or community member. A defaulter is defined as a patient who has not attended any NCD clinic appointments within the last 90 days, is not known to have died or moved out of the area, and has not been successfully contacted by phone on two occasions by the clinic registrar. The definition was changed in October 2016 to reflect the newly extended appointment interval for stable patients to: two consecutive missed appointments; not known to have died, moved out of the area, or become immobile and ineligible for home care; and has not been successfully contacted by phone on two occasions by the clinic registrar.

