### 3.4.6 Clinical audit

A paper-based checklist (Annexe 2d) will be used by a trained clinical staff member(s) to evaluate a sample of two hundred patient files with ten per cent of the sample cross-checked by the medical supervisor. A randomly selected sample of files of patients enrolled in the programme for over 12 months will be used. In addition, 65 files (based on a precision of 10%) from amongst the patients with asthma will be randomly selected, since the active cohort contains fewer than 300 patients diagnosed with asthma. The data will be anonymised, entered by a trained data entry operator into a password-protected Excel software database, analysed using proportions measured with Pearson’s χ2 test and reported with 95% confidence intervals.

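### The household survey was drawn in clusters, but section 3.6.4 tests it for Reach with an ordinary Pearson chi-square, so p-values for comparisons between areas will be too small

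*Protocol*

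**What the plan says.** **Design.** The Executive Summary describes the surveyed households as "selected using a two-stage cluster design". Section 3.6.2 says the same ("A two-stage cluster sampling methodology was adapted from the standardised methodology recommended by the WHO") and gives the size: "An estimated number of 2616 households needed to be interviewed, sampled in 327 clusters of eight households". Section 4.4 adds that different members of a household were interviewed for different subsections. Respondents therefore sit within households, and households within clusters.

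**Analysis.** Section 3.6.4 covers the secondary analysis used for Reach: eligibility for and receipt of NCD care, geographical reach, and knowledge of MSF. The stated method is: "Results will be analysed using basic descriptive statistics, including Pearson" chi-square tests for proportions, with p-values. Cluster adjustment, weights, a design effect and confidence intervals are not mentioned.

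**Executive Summary.** Its data-analysis paragraph gives a different method for the same work: "Secondary analysis of the pre-existing household survey data will use descriptive methods and multivariate regression modelling". In section 3.6.4, regression belongs to the completed primary analysis, and the secondary analysis has none.

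**The concern.** Pearson's chi-square is valid when observations are independent. In a cluster sample, neighbours tend to resemble each other, so each further respondent in a cluster adds less information than an independent one. The ordinary test ignores this.

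The outcomes in section 3.6.4 are of the exposed kind. Section 3.1 places both clinics in Irbid city centre and says that 40% of the refugees live in rural areas, so access to the service and awareness of it could well vary by place. Area is constant within a cluster, which is where ignoring the clustering does most damage. Reach is the first of the five objectives, and this survey is the first data source listed for it. Differences in coverage or awareness between areas could be called significant on weaker evidence than the p-value suggests.

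**Working it through.** **1. The protocol's own figure.** 327 clusters × 8 households = 2616 households, as stated in section 3.6.2. The reference proportion, precision and design effect behind 2616 are not given, so only this product can be checked.

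**2. Inputs for the size of the problem.** The number of respondents per cluster, *m*, is assumed to be 8, one per household. The true number is unknown: the NCD questions went only to adults with a listed condition, and a household may hold none or several. The ICC is also an assumption, taken from 0.01 to 0.20.

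**3. Formulas.**
- Design effect: DEFF = 1 + (*m* − 1) × ICC.
- True rejection rate of a nominal two-sided 5% unadjusted test, for a factor constant within clusters: 2 × [1 − Φ(1.96/√DEFF)].
- Effective sample size: 2616/DEFF.

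**4. Results for *m* = 8.**

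| ICC (assumed) | DEFF | √DEFF | True rejection rate | Effective n of 2616 |
|---|---|---|---|---|
| 0.01 | 1 + 7 × 0.01 = 1.07 | 1.03 | 5.8% | 2445 |
| 0.05 | 1 + 7 × 0.05 = 1.35 | 1.16 | 9.2% | 1938 |
| 0.10 | 1 + 7 × 0.10 = 1.70 | 1.30 | 13.3% | 1539 |
| 0.20 | 1 + 7 × 0.20 = 2.40 | 1.55 | 20.6% | 1090 |

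For example, at ICC 0.05: 1.96/1.162 = 1.687, which gives a two-sided tail of 9.2%.

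**5. Sensitivity to respondents per cluster.** At ICC 0.05, *m* = 4 gives DEFF 1.15 and a rejection rate of 6.8%; *m* = 16 gives 1.75 and 13.8%. Over ICC 0.01 to 0.20, DEFF runs from 1.03 to 1.60 for *m* = 4 and from 1.15 to 4.00 for *m* = 16.

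**6. Scope.** These rates hold for factors that do not vary within a cluster. For groups mixed within clusters, such as the sexes, the inflation is smaller and may be absent.

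**The case against.** **The effect may be trivial.** No ICC is given, and at 0.01 the true rate is only 5.8%. This stands as a limit on what can be claimed. The effect becomes material from an ICC of about 0.05.

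**The analysis is secondary and descriptive.** Section 1.1.6 treats the survey as initial information on reach, cohort and qualitative data also feed this objective, and no decision hangs on a p-value. This stands and lowers the severity. It does not remove the point, because section 3.6.4 does promise p-values.

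**Variance estimation can be left to a statistical analysis plan.** The wording of section 3.6.4 is not exhaustive, and Rao-Scott is itself a correction of Pearson's statistic. This stands in part: the fix refines the stated test. But the protocol names a specific test, and read as written it does not match the sample described in section 3.6.2.

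**Stronger readings that the protocol does not support.**
- A reader might infer that the planned survey confidence intervals will be too narrow. Section 3.6.4 promises none, so the direct harm is to p-values.
- A reader might infer that the absence of weights is an error. No selection probabilities are given, so the need for weights cannot be judged.
- A reader might infer that the completed primary analysis ignored the clusters. It is to be reported elsewhere, and the protocol does not say how clustering was handled.
- A reader might infer the same fault in the clinical audit, which is "analysed using proportions measured with Pearson" chi-square tests while one indicator counts "times when appropriate clinical action taken based on clinical or laboratory findings according to guideline". The checklist in Annex 2e records one answer per item per file, so each item-level percentage has one observation per patient. Only items 1.2, 1.9, 2.2 and 3.2 concern action on a finding. Item 2.2 applies to patients not known to be diabetic, so a file contributes at most three. Nothing says that the items are pooled. If two or three were pooled at an assumed ICC of 0.2, the design effect would be only 1.2 (1 + 1 × 0.2) to 1.4 (1 + 2 × 0.2).

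**Conclusion.** The point holds for the household survey alone. The protocol describes a two-stage cluster sample and fixes an analysis that assumes independent respondents. Followed as written, it gives p-values that are too small for comparisons by area or other cluster-level factors. The mismatch is plain in the text, but its size is less certain: about 6% to 21% true rejection for a nominal 5% test, resting on an assumed 8 respondents per cluster and an assumed ICC of 0.01 to 0.20.

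The disagreement with the Executive Summary over regression is separate and minor, but it concerns the same analysis and is best settled in the same edit. Overall this should be fixed before the survey results are reported. It does not threaten the evaluation as a whole.

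**What to change.** Amend section 3.6.4 so that:
- the survey is analysed by its design, with the cluster as primary sampling unit, and with weights where selection probabilities differ;
- proportions are compared with Rao-Scott chi-square tests;
- eligibility, coverage and knowledge of MSF are each reported with a design-based 95% confidence interval, as befits estimation questions and in line with the intervals already promised for the cohort, audit and adherence components;
- the text agrees with the Executive Summary on regression. If a model is kept, fit it with the survey design; otherwise remove it from the summary.

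The cost is about one paragraph and the use of survey-design functions in R, which section 3.6.4 already names. No new data collection is needed; the cluster identifiers, and the selection probabilities if weights are used, must be in the analysis file. P-values will be somewhat larger, and intervals somewhat wider than unadjusted ones would be.

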## 3.7 Qualitative research

The objective of the qualitative research is to explore key issues related to adoption, implementation and maintenance of the intervention, with a particular focus on the both the NCD guideline implementation and the MHPSS service.

### 3.7.1 Qualitative methods

Focus group discussions, semi-structured interviews, key stakeholder interviews, and participant observation will be used. Two same-sex focus groups will be conducted with NCD patients. These will explore the reach and implementation of the NCD model (e.g. perceived benefits, acceptability, barriers, unintended consequences). Topics will include examination of specific components of the NCD care (e.g. service provision, clinical consultation, medication adherence, health education, MHPSS and/or support from the HLO, the home visit service). These focus groups will then be followed at a later date (e.g. the following week) by semi-structured interviews with purposively selected focus group participants and other patients in order to explore further key issues raised in the focus groups, while ensuring that patients accessing each element of the service are represented.

Semi-structured interviews will also be conducted with health care staff involved in the NCD services. These will focus particularly on issues related to: (i) reach (e.g. available resources and support, perceived benefits versus costs, barriers, suggestions for improvement; and (ii) adoption and implementation (e.g. values and capacity, implementation challenges and adaptations, compatibility with values, resources, complexity); (iii) maintenance: support, activities to support sustainability, perceived benefits vs. costs. The interviews will include a focus on specific components of NCD care (e.g. service provision, clinical consultation, medication prescription and adherence, health education, MHPSS and/or support from the HLO, home visit service). Key stakeholder interviews will be conducted with Syrian refugee community leaders, representatives from the MoH and other NGOs. Participant observation will be undertaken at clinics.

### 3.7.2 Qualitative research study population and sampling

Information about the study will be provided to all patients attending both MSF NCD clinics in Irbid using posters and leaflets and discussion during group education and counselling sessions. Two same-sex focus groups of approximately eight people each will be conducted with a cross-section of NCD outpatients, aged 18 or above, including a mix of patients attending either of the two MSF clinics. Patient selection will be based on NCD type and severity, age, gender and literacy as suggested by MSF clinical staff.

These focus groups will be followed by individual semi-structured interviews. Some participants of the focus groups who had particularly insightful perspectives will be purposively selected for individual interviews by the principal investigator and local study coordinator in order to follow-up on key issues raised. Specific permission to re-contact focus group participants and the right to withdraw this consent will be included in consent forms. The research coordinator will separately record the participant’s preferred means of contact to protect their confidentiality.

Patients attending either clinic will be approached in the waiting room by the local research coordinator, informed about the study and invited to participate in focus groups and /or individual interviews. Approximately 12 or more individual interviews with NCD patients recruited from both clinic sites will be conducted, aiming to include patients who have accessed each component of the NCD service (including HLO, home visit service, MHPSS). This is subject to principles of saturation.

Approximately 12 semi-structured interviews will be conducted with key staff involved in the provision of NCD care in either of the two MSF clinics. These staff will be purposively selected to reflect the range of activities and staff functions involved. They may include the doctors and nurses, psychosocial workers, field co-ordinator, and expatriate MSF medical and research staff in Irbid and internationally either currently or previously involved in the NCD programme. Participants will be eligible if they are full-time members of staff (i.e. not temporary workers) and have worked in the NCD clinic, in the MSF Irbid NCD project office or as MSF Jordan country coordination or headquarters staff from December 2014 to the present for a minimum of three months.

Approximately six key stakeholder interviews will be conducted with Syrian refugee community leaders and with representatives of the Ministry of Health and District Health Office who are involved in NCD care delivery. The community leaders, identified during the MSF household survey and through the MSF Irbid team’s community engagement work, will be invited to an interactive information meeting where they will be invited to participate in interviews. If more than three people volunteer, three names will be selected at random using Microsoft Excel.

